### Sample Size

To detect a difference of 1 point between the two groups on the pain level scales, a sample of 50 patients is required, with 25 in each group, assuming an SD of 3 points, a 95% confidence level, a Z-score of 1.96, a margin of error *α*<.05, and an estimated 10% dropout rate [15].

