**Methods:**

This randomized, controlled, multicenter, open-label trial involves two groups: an intervention group receiving VR sessions and a control group receiving standard pharmacological treatment. Participants are adults aged 30‐61 years diagnosed with neuropathic pain, unresponsive to flexible doses of gabapentin. Pain and anxiety levels are assessed using the Pain Detect Questionnaire, Visual Analog Scale (VAS), and Goldberg Anxiety Scale at baseline and follow-up points. VR sessions are conducted weekly for 3 weeks, each lasting 30‐35 minutes. Perceived time during VR sessions is recorded as an indirect measure of distraction effectiveness. The primary outcome is the reduction in pain intensity and anxiety levels post-intervention compared to baseline. A sample size of 30 patients (15 per group) was calculated to achieve 80% statistical power, considering a 2-point mean difference in VAS scores.

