### Data Collection, Sources of Information, and Intervention

Pain intensity will be measured using the PainDETECT Questionnaire [13], which is self-administered with 9 descriptors. It detects neuropathic pain intensity and discriminates between possible neuropathic pain (scores between 12 and 19) and definite neuropathic pain (scores above 19). The Visual Analog Scale (VAS) is a one-dimensional quantitative, effective, and easily reproducible scale. Patients mark a 100-mm segment with endpoints labeled as no pain (0 mm) and maximum pain (100 mm); the measure from 0 to the patient-marked point indicates pain intensity. A change of 20 mm (or 2 points on a 10-point pain intensity scale) is considered clinically significant.

Anxiety will be measured using the Goldberg Anxiety Scale [14], a test that not only guides diagnosis but also measures intensity. It contains 2 subscales with 9 questions each: anxiety subscale (questions 1‐9). The first 4 questions of each subscale (questions 1‐4) act as a precondition to determine if the rest of the questions should be answered. Specifically, if fewer than 2 questions of the first 4 are answered affirmatively, the rest of the first subscale questions should not be answered. For the second subscale, it is sufficient to answer one of the questions 10‐13 affirmatively to proceed with the rest of the questions.

Time perception will be analyzed as an indirect measure of distraction, with less attention to pain, greater tolerance, and possibly an early sensation of completing the treatment time (or Tprogrammed).

At the end of each VR session (30 to 35 minutes), patients will be asked how much time they think remains. This is called “perceived time” (Tperceived) and will be recorded in 10‐15-minute intervals based on their responses.

A “significant” difference is defined as a time difference (Tprogrammed - Tperceived) of ≥15 min and “no change” if ≤10 min. For patients who request to stop before completing the time, their “perceived time” is noted by adding the remaining time to the total programmed time.

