### Patient Recruitment for Study Participation

#### Patient Selection

Patients included in the study will be selected from individuals diagnosed with persistent neuropathic pain by Pain Units, with moderate to severe intensity. All will be duly informed about the nature and objectives of the study.

Twenty-five patients will be included, and their scores on the VAS, the Pain Detect Questionnaire, and perceived time will be analyzed.

Participants will be adults aged 30 to 61 years. This age range was selected to reduce clinical variability and cognitive interference associated with younger or older populations. Individuals aged under 30 years may not reflect the target patient population for chronic neuropathic pain in clinical practice, while individuals aged over 61 years may present comorbidities or age-related cognitive decline that could interfere with VR engagement or outcome assessments.

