### Statistical Analysis

Subjects will be analyzed according to the group to which they were assigned.

Data will be collected through Microsoft Forms (an application included in Office 365 by Microsoft Corporation that allows for creating customized questionnaires, surveys, and records) and analyzed with R software (version 4.0.3). Categorical variables will be described using absolute frequencies and percentages, and continuous variables will be described using means and standard deviations or medians and quartiles. A two-tailed *t* test will be used to compare values related to pain, anxiety, and satisfaction between the two groups. Correlations between pain perception and anxiety values reported by patients will be assessed using Pearson’s correlation. The significance level will be set at 5%, and all confidence intervals will be set at 95%.

Data will be stored in a database. Pearson’s *χ*^2^ test will be used to calculate statistical significance.

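### The 50 patients said to be required for a 1-point difference give about 21% power on the stated inputs, and the abstract reports an incompatible calculation (30 patients, 2 points)

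*Protocol article*

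**What the plan says.** The protocol article justifies its size in two places.

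- **Methods, Sample Size:** "To detect a difference of 1 point between the two groups on the pain level scales, a sample of 50 patients is required". The split is 25 per group, "assuming an SD of 3 points, a 95% confidence level, a Z-score of 1.96", with alpha 0.05 and an expected dropout of 10%. No power is given, and the scale is not singled out.
- **Abstract, Methods:** "A sample size of 30 patients (15 per group) was calculated to achieve 80% statistical power". The effect there is a 2-point mean difference on the VAS. No SD and no dropout rate are given.

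The Statistical Analysis section fixes the test that both must serve: "A two-tailed *t* test will be used to compare values related to pain", at the 5% level, between the two groups.

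**The concern.** A sample-size statement should follow from its own inputs. In the Sample Size section the target difference is one third of an SD (1/3), which normally needs well over 100 patients per group, so 25 looked far too few. The abstract has a smaller trial, a larger effect and a power figure, so the two passages cannot come from one calculation.

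The stake is how the result will be read. If the article says that 50 patients suffice to detect 1 point, a non-significant result looks informative about a 1-point effect. On the stated inputs the trial would miss such an effect about four times in five. A reader also cannot tell whether 30 or 50 is the recruitment target.

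**Working it through.** **Inputs.** From Sample Size: difference δ = 1, SD σ = 3, z = 1.96, dropout 10%, n = 25 per group. From Statistical Analysis: two-tailed two-group t test at 5%. From the abstract: δ = 2, n = 15 per group, power 80%. Assumption: the points are on the 10-point pain scale.

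**1. Trying to reproduce 25 per group.** With n per group = 2σ²(z₁₋α/₂ + z₁₋β)²/δ²:

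- 80% power (borrowed from the abstract): 2 × 9 × (1.96 + 0.84)² / 1² ≈ 141.3, so 142 per group; the t test gives 142.2. Allowing for dropout: 142/0.9 ≈ 158 per group, 316 in total.
- 50% power: 2 × 9 × 1.96² ≈ 69.1, so 70 per group.
- One-sided 5%, 80% power: 112 per group. One-sided 5%, 50% power: 49 per group.
- One-sample precision formula, (1.96 × 3 / 1)² = 34.6; with dropout about 38.
- One-sample test at 80% power: 71.

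None of these gives 25 per group or 50 in total.

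**2. Power of the stated design for 1 point.**

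- Standard error at 25 per group: 3 × √(2/25) = 0.849. Noncentrality: 1/0.849 = 1.18. Critical t on 48 df: 2.01. Power: **21.1%** (about 22% by the normal approximation).
- After 10% dropout, 25 × 0.9 = 22.5 per group. Power is **19.1%** at 22 and 19.8% at 23.
- The 95% confidence interval half-width at 25 per group is 2.01 × 0.849 = 1.71 points. An observed difference of exactly 1 point gives t = 1.18 and p = 0.24.

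**3. The abstract's figure.**

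- The SD at which 15 per group has 80% power for 2 points is 1.89 by the t test (1.96 by the normal formula).
- At SD 3 the power for 2 points with 15 per group is 42%.

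**4. What 50 patients support at SD 3, two-sided 5%, t test.**

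| Evaluable per group | Difference with 80% power | Power for 2 points | Power for 1 point |
|---|---|---|---|
| 25 | 2.43 | 64% | 21% |
| 22 | 2.59 | 58% | 19% |

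**The case against.** The strongest reply is that this is a condensed article. The Sample Size section names no power, so 80% is being imposed on it, and the full calculation may sit elsewhere. The first part is fair: leaving out the power is not itself the defect, and 80% is borrowed from the abstract. But the result does not hang on that choice, because 25 per group falls well short of the 70 needed even for 50% power. An unstated adjustment for baseline would not rescue it either: at assumed correlations of 0.5 and 0.7, power for 1 point at 25 per group is about 27% and 38%.

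Four stronger readings are tempting, and the article does not support them.

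- **That the abstract is arithmetically wrong.** It gives no SD, and its claim is attainable at about 1.9. The 42% applies only if the SD of 3 is carried over. What is shown is that the two statements are incompatible.
- **That the two passages state different powers.** Only the abstract states one.
- **That Patient Selection adds a third total.** Its sentence "Twenty-five patients will be included" mentions perceived time, which is asked after VR sessions, and a separate Control Selection section follows. It most naturally means the VR group, which agrees with 25 per group.
- **That 1 point is a wrong target because it is half of the protocol's threshold.** The article says "A change of 20 mm (or 2 points on a 10-point pain intensity scale) is considered clinically significant", which speaks of a change, and its pilot results apply 2 points to individual patients. A between-group mean difference below that threshold can be a legitimate target.

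Nor does the article describe any plan to stop at 30 or at 50 according to the results. The conflict leaves the target unclear, and no more than that should be inferred.

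**Conclusion.** The point holds. On its own inputs the Sample Size section is wrong: 50 patients give about 21% power for 1 point, or about 19% after the expected dropout. The number per group is short by a factor of almost six against 80% power (142/25 ≈ 5.7). Separately, the section conflicts with the abstract on total (50 against 30) and on effect (1 against 2 points), and the abstract's claim implies an SD of about 1.9 where the section has 3.

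The power figures rest on the article's SD of 3, its two-tailed t test and equal groups. The 142 also rests on taking 80% as the intended power. The article does not show which total or which SD the authors intend, so this review cannot settle that for them.

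**What to change.** The authors should confirm which total governs, then use one calculation, identically worded, in the abstract and in Sample Size. It should state the scale, difference, SD, power, alpha and dropout.

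If 50 patients and SD 3 stand under the planned t test, delete the 1-point claim and the claim of 80% power with 30 patients, and write:

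> 50 randomised (25 per group), about 22 per group evaluable after 10% dropout, SD 3 on the 10-point pain scale, two-sided 5%: 80% power for a between-group difference of about 2.6 points, and about 58% power for 2 points.

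If another SD is intended, such as the roughly 1.9 implied by the abstract, state it, give its basis and recompute. If the authors instead want 80% power for 2 points at SD 3, the t test needs about 36.3 evaluable per group, or 36.3/0.9 ≈ 40.3 randomised per group (41 rounded up). That would be a larger trial.

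Restating the figure needs wording only and no extra patients. Its price is a less favourable stated power. The article describes the trial as still in its preparatory phase, so the correction can still be made early.

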### Patient Recruitment for Study Participation

#### Patient Selection

Patients included in the study will be selected from individuals diagnosed with persistent neuropathic pain by Pain Units, with moderate to severe intensity. All will be duly informed about the nature and objectives of the study.

Twenty-five patients will be included, and their scores on the VAS, the Pain Detect Questionnaire, and perceived time will be analyzed.

Participants will be adults aged 30 to 61 years. This age range was selected to reduce clinical variability and cognitive interference associated with younger or older populations. Individuals aged under 30 years may not reflect the target patient population for chronic neuropathic pain in clinical practice, while individuals aged over 61 years may present comorbidities or age-related cognitive decline that could interfere with VR engagement or outcome assessments.

#### Control Selection

Controls will be selected from patients in the Pain Unit diagnosed with moderate to severe neuropathic pain. All will be duly informed about the nature and objectives of the study and asked to provide signed consent.

Before the study begins, training on the use of the devices will be provided to all health care personnel involved.

#### Data Collection, Information Sources, and Intervention

Data collection will begin once the patient has provided written informed consent. Patient assignment to a study group will be randomized using the RandomizedR computer system.

The data collector will record the patients’ age, sex, study group, and type of intervention performed. Before contacting the patient with the virtual reality device, the patient’s status and heart rate will be recorded upon arrival at the clinic, regardless of the assigned study group.

Patients in Group 1 will be the intervention group. They will undergo 10 virtual reality pain treatment sessions (Monday to Friday for 2 weeks), with each session lasting 30 minutes, while maintaining treatment with gabapentin at a dose of 1200 mg/24 h. Their clinical history, pain situation, and anxiety will be assessed in each session.

Patients in Group 2 will be the control group. Their clinical history, pain situation, and anxiety will be assessed in each session. They will receive pain treatment with oral gabapentin at a dose of 1200 mg/24 h. The control group will receive standard care without any VR exposure. Participants will remain in a quiet room with standard analgesic treatment as prescribed. No additional relaxation stimuli will be provided. Outcome data will be collected in parallel with the intervention group.

Figure 2 shows the CONSORT diagram.

**Figure 2. F2:**
[figure not shown]
CONSORT diagram used in clinical trial reporting to track the flow of participants through a trial, showing how many were screened, eligible, randomized, and completed each stage of the study.

### Data Analysis

Data entry for anxiety and pain test scores through VAS, Pain Project, and perceived time will be performed using Microsoft Excel and analyzed using SPSS statistical software (version 16.0).

A sample *t* test will be used. Before applying the *t* test, the Kolmogorov-Smirnov test will be used to evaluate the normality of the mean scores obtained.

Likert-type statements will be analyzed such that a score below 3 indicates disagreement and a score above 3 indicates agreement with a positive statement and vice versa for a negative statement.

Intervention group patients will be informed that they can use the VR device. They will be assisted in putting on the device and given a brief explanation of the content to be displayed.

Data collected from the control group will be compared with those from the intervention group (heart rate, pain perception level, anxiety level).

The mentioned data will be collected by an IT professional through a web questionnaire generated by Microsoft Forms on a tablet and will be stored on a computer server.

### Statistical Analysis

Subjects will be analyzed according to the group to which they were assigned.

Data will be collected through Microsoft Forms (an application included in Office 365 by Microsoft Corporation that allows for creating customized questionnaires, surveys, and records) and analyzed with R software (version 4.0.3). Categorical variables will be described using absolute frequencies and percentages, and continuous variables will be described using means and standard deviations or medians and quartiles. A two-tailed *t* test will be used to compare values related to pain, anxiety, and satisfaction between the two groups. Correlations between pain perception and anxiety values reported by patients will be assessed using Pearson’s correlation. The significance level will be set at 5%, and all confidence intervals will be set at 95%.

Data will be stored in a database. Pearson’s *χ*^2^ test will be used to calculate statistical significance.

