## Discussion

### Principal Findings

This protocol outlines a randomized controlled trial aimed at evaluating the impact of VR on reducing anxiety and chronic neuropathic pain. Based on a previous pilot study and literature supporting the use of immersive distraction therapies [6,8,10], we hypothesize that VR will significantly improve patient-reported outcomes in terms of pain perception, anxiety levels, and treatment satisfaction.

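### The planned pain–anxiety correlation has no term for study group; if post-treatment values from both arms are pooled, part of any VR effect on both scores is counted as patient-level association (minor, free to correct).

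*Protocol article*

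**What the plan says.** The Statistical Analysis section of the protocol article first describes the group comparison: "A two-tailed *t* test will be used to compare values related to pain, anxiety, and satisfaction between the two groups". The next sentence gives the correlation: "Correlations between pain perception and anxiety values reported by patients will be assessed using Pearson’s correlation". The first sentence names the two groups and the second does not. The correlation sentence also leaves open the time point, whether raw or change scores are used, and what the coefficient is meant to show. The section's 5% significance level follows directly.

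Both arms supply the data. Under Data Collection, Information Sources, and Intervention, the same statement is made for Group 1 and for Group 2: "Their clinical history, pain situation, and anxiety will be assessed in each session".

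The trial expects VR to move both variables. Under Principal Findings: "we hypothesize that VR will significantly improve patient-reported outcomes in terms of pain perception, anxiety levels, and treatment satisfaction". The Conclusions of the abstract say the same for pain and anxiety.

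**The concern.** Pearson's test for zero correlation assumes a single homogeneous sample of independent pairs. Post-treatment values from two randomised arms are a mixture of two samples, and the trial hopes that their means differ on both variables. If VR lowers both, the VR patients sit lower on both scores and the controls higher. The pooled scatter then slopes upward even if, within each arm, a patient's pain says nothing about that patient's anxiety. The coefficient and its p-value would partly restate the treatment effect that the *t* tests already report.

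What is at stake is the meaning of a secondary result. The Introduction motivates the trial by the coexistence of neuropathic pain and affective symptoms, so a significant r could be taken as support for that link. The distortion is largest when VR works well on both scores.

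**Working it through.** **Inputs from the protocol article**

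- Sample Size: a 1-point difference; "a sample of 50 patients is required, with 25 in each group, assuming an SD of 3 points". This gives d = 1/3 = 0.33.
- Data Collection, Sources of Information, and Intervention: "A change of 20 mm (or 2 points on a 10-point pain intensity scale) is considered clinically significant". With the SD of 3 from Sample Size, d = 2/3 = 0.67. Combining these two figures is an assumption.
- Abstract, Methods: "A sample size of 30 patients (15 per group) was calculated to achieve 80% statistical power, considering a 2-point mean difference in VAS scores". No SD is given there.

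**Assumptions, because the article gives no figure**

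- The VR effect on anxiety, in SD units, equals the effect on pain, except where stated.
- The within-arm correlation ρ is 0, except where stated.
- Final values are used, one pair per patient, with both arms pooled.

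**Plan's own figure.** The article states no r, sample size or power for the correlation, so there is nothing to reproduce. For the abstract's design, solving the two-sided two-sample *t*-test power equation with 15 per group, 80% power and α = 0.05 gives d = 1.06, which corresponds to an SD of 2/1.06 = 1.89. The two sample-size statements disagree with each other, but this point does not depend on that, so both are used as separate scenarios.

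**Formula.** With 1:1 allocation, unit within-arm SD and shifts d₁ (pain) and d₂ (anxiety), the arm difference adds d₁d₂/4 to the covariance and d²/4 to each variance:

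r(pooled) = (ρ + d₁d₂/4) / √[(1 + d₁²/4)(1 + d₂²/4)]

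**Numbers at ρ = 0, equal shifts**

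- d = 0.33: 0.0278/1.0278 = 0.03
- d = 0.67: 0.1111/1.1111 = 0.10
- d = 1.06: 0.2809/1.2809 = 0.22

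**Rejection rates** (simulation, two-sided 5%, independent normal pain and anxiety within arm; partial correlation tested on N − 3 degrees of freedom)

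| Effect on both scores | Pooled r | N = 30, pooled | N = 50, pooled | Adjusted for arm |
|---|---|---|---|---|
| 0.33 (1 point, SD 3) | 0.03 | 5.2% | 5.3% | about 5% |
| 0.67 (2 points, SD 3) | 0.10 | about 8% | 10 to 11% | about 5% |
| 1.06 (abstract's design) | 0.22 | about 22% | not used | about 5% |

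The last row is shown only at 30 patients because d = 1.06 is derived from that sample size.

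**Sensitivity to the assumptions**

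- Smaller anxiety effect: with 0.67 on pain and 0.33 on anxiety, r = 0.0556/√(1.1111 × 1.0278) = 0.05, and rejection at N = 50 is between 6% and 7%.
- Real within-arm association, ρ = 0.5: r = (0.5 + 0.0278)/1.0278 = 0.51 at d = 0.33 on both, and (0.5 + 0.1111)/1.1111 = 0.55 at d = 0.67 on both.
- Effect on pain only, ρ = 0.5, d₁ = 0.67: r = 0.5/√1.1111 = 0.47, so the coefficient is slightly diluted instead.

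**The case against.** The article does not say that the arms are pooled. The plural in the correlation sentence fits coefficients by arm or by visit, and a baseline or within-arm correlation would not have this problem. The article states no hypothesis for r and no interpretation of it; the objective and primary outcome concern reductions in pain and anxiety. A pooled r is a valid description of overall association and misleads only if read as a patient-level link. Arm and time point for a secondary correlation are also commonly left to a fuller document, which is not shown.

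Most of this stands, and it limits the point to a minor one. It does not remove it. The sentence names an unadjusted method and omits the groups immediately after a sentence that names them, so pooling remains the natural reading. Under the trial's own hypothesis, a better method is available at almost no cost.

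Two stronger readings are tempting. First, because both scores are taken at each session, a reader might infer that every session's pair will be entered as an independent observation. Nothing in the article says so. Second, a reader might apply the abstract's implied effect of 1.06 SD to the 50 patients of the Sample Size section and obtain a higher error rate. No design in the article has that combination: 1.06 follows from 30 patients, and the 50-patient statement goes with 1 point and SD 3, where the distortion is negligible.

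**Conclusion.** The point holds as a minor improvement. Read as pooling both arms after treatment, the planned correlation overstates patient-level association whenever VR lowers both scores. The excess in r runs from about 0.03 at 1 point and SD 3 to about 0.22 at the effect implied by the abstract. Rejection of a true zero within-arm correlation runs from about 5% to about 22%, with 8% (N = 30) and 10 to 11% (N = 50) in between at 2 points and SD 3.

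These sizes rest on an assumed anxiety effect equal to the pain effect and on zero within-arm correlation. A smaller anxiety effect reduces the excess, and if pain and anxiety are truly correlated at 0.5 the shift is 0.01 to 0.05 at d = 0.33 to 0.67. The documents do not support saying that the trial will report a false patient-level link, since neither pooling nor that interpretation is stated. The between-group comparison of pain and anxiety does not use this coefficient and is not affected.

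**What to change.** Replace the correlation sentence with wording such as: *The correlation between pain (VAS) and anxiety (Goldberg) will be computed with one pair of values per patient at [stated time point], as a partial correlation adjusted for study group, with a 95% confidence interval.* If the question is whether improvements go together, use each patient's change from baseline in both scores, again adjusted for study group.

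The cost is one sentence and one degree of freedom. No new data, visits or patients are needed.
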